**Fig. 3 fig3:**
[figure not shown]
(A) Assembly process showing two 3D-Screens and a wooden frame. (B) Final configuration of the 3D-WDS setup, with screens mounted on either side of the frame. (C) Front view of a completed 3D-WDS unit. (D) Lateral view showing the conical structure of the screen material. (E) Application on a typical mud house. Mosquitoes are attracted to host odors and CO_2_ from inside the house and enter through open eaves and windows. Those entering through windows are trapped between the screens. Those entering through eaves and attempting to exit via windows after feeding are also trapped, thereby reducing malaria transmission potential.

**Fig. 4 fig4:**
[figure not shown]
Real-world components and installation of 3D-WDS in the study area. (A) Injection-molded plastic cone (right) and its corresponding mounting ring (left), which includes integrated hooks for fastening the cone onto the mesh screen. (B) A trained community carpenter assembling the 3D-WDS by attaching cones to the mesh using mounting rings. (C) Fully installed 3D-WDS units on the window frames of a traditional mud-plastered house in the study area.

### Participant withdrawal and ethical considerations

2.4

The study ensured that participants had the freedom to withdraw from the study at any point, without providing an explanation. In the event that the homeowners requested their house to be restored to the pre-intervention state, any 3D-WDS installed were taken down and replaced with the original structure. Withdrawals could also occur, if a child from the participating household had any clinical abnormalities, intercurrent illness, or other medical condition or situation that occurred so that continued participation in the study was not in the best interest of the participant. If at least one child was not consistently available for the cross-sectional surveys in a household, that household became ineligible for participation, and the related data was excluded from the analyses. If a household withdrew consent, no further follow-up was made in that household. If this household was participating in the entomology collections (done in a randomly selected subset of households; details below), it was replaced by a neighbouring participant household. The study team made sure that they respected the participants' rights and ensured that there were contingency plans in place for any unforeseen events that might compromise the study's validity.

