### Trial design

1.3

An overview of the trial design is summarised as flowchart in Fig. 1 and the schedule of the trial activities is presented in Table 3. The study was designed as a two-arm cRCT with hamlets as the unit of randomization. The outcome measurements were conducted as repeated cross-sectional surveys of malaria and anaemia prevalence, indoor mosquito densities and entomological inoculation rate. Twenty hamlets (clusters) from 17 villages across Muheza District in the northeast of Tanzania were selected during the mapping of study area. The selection was primarily based on logistics and transport feasibility, population size and number of houses in the candidate clusters. Followed by community sensitization, a baseline survey was conducted to assess the socio-demographic profile of the candidate clusters, malaria prevalence, indoor malaria vector densities and level of insecticide resistance in candidate clusters. Fourteen clusters from the 20 candidate clusters were selected based on comparability in malaria prevalence, vector densities, and insecticide resistance profiles, to ensure balanced baseline characteristics across study arms. These 14 clusters were then randomly allocated: seven to the control arm, which received universal coverage of LLINs, and seven to the intervention arm, which received 3D-WDS installations in addition to LLINs. In both arms, existing LLINs were supplemented as needed to achieve universal coverage. Worn-out nets (e.g., those with holes) and nets estimated to be more than two years old were replaced to ensure adequate protection in all participating households. The target coverage for 3D-WDS in the intervention arm was ≥80 % of all houses in the intervention clusters. Follow-up cross sectional surveys began after the installation of intervention and LLINs rollout. Epidemiological and entomological data were collected every 10 weeks through cross-sectional surveys and ancillary social studies were conducted midway through the trial and during the final observation weeks of a 50-week follow-up period. Malariometric surveys were conducted by examining one or more children aged 6 months to 14 years living in the participating house for malaria, anaemia and general health conditions. Exposure to malaria vectors were measured using Centres for Disease Control and Prevention (CDC) miniature light traps (CDC-LTs) in both control and intervention arm. Mosquito collections were morphologically identified to species level and subjected to molecular analysis for sibling species identification, *Plasmodium* parasite and sporozoite infectivity, blood meal sources and L1014S knockdown resistance-East (*kdr*E) mutations against pyrethroids. Household and community acceptability of the 3D-WDS were assessed by organizing a series of focus group discussions (FGDs), interviews and community observation midway through the trial and during the final observation weeks of the trial. Data collections were carried out on electronic devices and stored on a secure cloud server for further processing.

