All households in the intervention clusters were first assessed for eligibility based on predefined inclusion criteria, the main one being the presence of at least one child aged 6 months to 14 years. Additional considerations, such as the structural suitability of the house for 3D-WDS installation, were also applied. Households meeting these criteria were approached for consent to participate in the study, which included both the installation of the 3D-WDS and the screening of eligible children for malaria. Only households that provided informed consent were registered and assigned a unique household identification number. Refusals were rare—only two households declined participation across the seven intervention clusters.

Household registrations were conducted during the sensitization meetings, and each participating house was marked with its unique ID number. The same registered households were approached during each survey round for epidemiological follow-up. From each household, a child aged 6 months to 14 years was enrolled. If the previously screened child was unavailable, another eligible child from the same household was examined. This approach ensured consistency in sampling at the household level while allowing flexibility at the individual level.

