### Participant timeline

2.8

The study spanned 2 years and 7 months (April 2019 to October 2021). The initial 6 months were dedicated to site selection, community engagement and the baseline survey. An additional 7 months were allocated for cluster formation and randomization, training of installers, installation of the 3D-WDS and distribution of LLINs. The cRCT itself lasted approximately 12 months, followed by a 3-month close-out stage.

The baseline survey began in May 2019, alongside community sensitization and a sociodemographic survey. Baseline entomological and epidemiological surveys were conducted in parallel during June and July 2019. Insecticide resistance surveys were carried out shortly after the long rainy season, between July and August 2019.

Cluster formation and randomization occurred in late August 2019, followed by the recruitment of installers and workshop training for 3D-WDS installation in September 2019. The installation process took 5 months (October 2019 to February 2020), and LLINs distribution occurred in early March 2020.

Epidemiological and entomological follow-up assessments were conducted in parallel through repeated cross-sectional surveys from April–May 2020 to June–July 2021, at intervals of 10, 20, 30, 40 and 50 (±2) weeks post-intervention. The epidemiological team visited one cluster per day during each follow-up survey (14 days for 14 clusters), examining children for malaria infection and anaemia. Entomological surveys involved randomly selecting 24 houses per cluster over six nights, with samples collected from four houses each night.

Ancillary social studies were conducted through FGDs and household interviews at 30, 40, and 50 (±2) weeks post-installation to assess the community's acceptance of the 3D-WDS. Screen integrity, maintenance and durability were also evaluated during these surveys.

The schedule of pre-intervention activities, baseline cross-sectional and post-intervention follow-up surveys are outlined in the table below (Table 3).

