#### Intervention effects

2.14.3

Intervention effects on patient outcomes will be assessed in a multivariate model that also includes the baseline variables specified above, including controlling for age and monthly precipitation squared. These intervention models will use data from all post-intervention surveys and will include time since baseline as a predictor variable, to allow for potential gradual or cumulative effects over the course of follow-up. Intervention/control will be included in these models as a main effect and also in interaction with time, allowing outcomes to change through time in one group but not in the other (e.g. a gradual decrease in malaria prevalence in intervention clusters vs. no change in control clusters). If the interaction will not be significant, it will be removed from the model and the main effect of intervention assessed.

In addition, we will test for any overall or intervention-driven change from baseline to post-intervention by pooling all post-intervention surveys and testing for an interaction between intervention. Due to the distribution of bed nets as part of the protocol, it will be possible that all participating households would experience a reduction in epidemiological or entomological outcomes, but that the reduction would be even bigger for households receiving 3D-WDS intervention.

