#### Model structure

2.14.4

All statistical modelling will be done with mixed-effects models, using the lme4 package in R [40]. All models of patient outcomes will include a random effect (random intercept) of household nested within cluster. This will allow for non-independence of sampling units by allowing the response variable to vary between clusters and in addition between households, not in association to any of the modelled fixed effects but in relation to any unobserved sources of structured error. Child ID will not be included as a random effect because the spontaneous nature of which children each household presented for examination at each visit meant that few children will be resampled often enough to be able to informatively model the individual-level variation. Baseline models will be fitted using only cluster ID as the random effect, due to limited sample sizes within each household. Malaria prevalence as measured by mRDT will be modelled in a binomial model with a logit link, and haemoglobin level will be modelled in a Gaussian model with an identity link.

Indoor mosquito densities and EIR will be analyzed at the level of clusters, using total counts of 24-night CDC-LTs collections per cluster in every cross-sectional survey. Hence, the models will include only a random effect (random intercept) of cluster ID. Count data will be modelled in a Poisson model with a log link; potential overdispersion will be accounted for by including an observation-level random effect. EIR will be modelled in a binomial model with a logit link weighted by the number of mosquitoes caught in each sample.

Community members’ perceptions will be qualitatively analyzed using data from questionnaires, focus group discussions and in-depth interviews. Additionally, quantitative data from the household questionnaire survey will be summarised using appropriate descriptive statistics.

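### Leaving households out of the analyses because no child was consistently available is a post-randomisation exclusion that could bias the primary malaria comparison and discards usable results

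*Protocol article*

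**What the plan says.** The rule is in section 2.4 (Participant withdrawal and ethical considerations): "If at least one child was not consistently available for the cross-sectional surveys in a household, that household became ineligible for participation". The consequence in full is "that household became ineligible for participation, and the related data was excluded from the analyses". Given the child-substitution rule below, I read the trigger as no child of the household being consistently available. The article does not say how many missed rounds count, or whether the related data are all of the household's records or only some. For withdrawn consent, the same section only stops further follow-up and does not say that earlier data are dropped.

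The other relevant statements are:

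- **Timing (2.8).** "Cluster formation and randomization occurred in late August 2019". Follow-up surveys ran "from April–May 2020 to June–July 2021, at intervals of 10, 20, 30, 40 and 50 (±2) weeks post-intervention".
- **Design (1.3).** "The outcome measurements were conducted as repeated cross-sectional surveys of malaria and anaemia prevalence".
- **Absent children (2.2.2).** "If the previously screened child was unavailable, another eligible child from the same household was examined".
- **Data in the models (2.14.3).** "These intervention models will use data from all post-intervention surveys".
- **Model (2.14.4).** "All models of patient outcomes will include a random effect (random intercept) of household nested within cluster".

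**The concern.** The rule settles who enters the primary analysis by something that happens after allocation. Allocation was visible: intervention houses had screens fitted, and control houses were left unmodified (2.3.1, 2.3.2). Only intervention households had screens inspected every 10 weeks (2.5), and half of those with screens were selected for structured interviews (2.10). Willingness to be present could therefore differ by arm. Illness or travel could affect both a child's presence and the mRDT result.

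If exclusion differs by arm, or acts differently by arm, and is related to infection, the retained households no longer give the comparison that randomisation set up. The article mentions no analysis with all households that would reveal this. The rule also has no evident purpose in this design. A household seen at three of five rounds gives three usable cross-sectional observations.

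**Working it through.** **1. Is the exclusion post-randomisation?** Randomisation was in late August 2019 and the first follow-up round was in April–May 2020 (2.8). Availability over follow-up cannot be known at allocation, so the answer is yes.

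**2. Does the design need complete household series?** No. Outcomes come from repeated cross-sections (1.3), and random intercepts for household and cluster (2.14.4) accept unequal numbers of rounds per household.

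**3. How many households could be caught?** No absence rate is given, so the rate q per round is assumed, independent over five rounds.

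- Excluded if one miss disqualifies: 1 − (1−q)^5
- Excluded if two or more misses are needed: 1 − (1−q)^5 − 5q(1−q)^4
- Share of collected records left out if one miss disqualifies and all of a household's records go: 1 − (1−q)^4

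| q | Excluded, one miss | Excluded, two or more | Records left out, one miss |
|---|---|---|---|
| 5% | 23% | 2% | 19% |
| 10% | 41% | 8% | 34% |
| 15% | 56% | 16% | 48% |

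**4. How large could the bias be?** Let P be the true prevalence in an arm, e the share of households excluded, and r the prevalence in excluded households divided by that in retained ones. Retained prevalence = P / [(1−e) + e·r]. Take no true effect, P = 0.44 in both arms (the control value in 2.9). The values of e and r are assumptions.

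- e = 10% control, 30% intervention, r = 1.5: 0.44/1.05 = 41.9% versus 0.44/1.15 = 38.3%. OR = (0.383/0.617)/(0.419/0.581) = 0.86.
- Same e, r = 0.67: 0.44/0.967 = 45.5% versus 0.44/0.901 = 48.8%. OR = 1.14.
- e = 10% control, 20% intervention: OR 0.92 (r = 1.5) or 1.07 (r = 0.67).
- Equal e and equal r in both arms: OR = 1.00.

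**5. What happens to power?** The plan's own figure comes first. The Hayes–Bennett formula is c = 1 + (1.96 + 0.84)² × [(p1(1−p1) + p2(1−p2))/m + CV²(p1² + p2²)]/(p1−p2)². The inputs from 2.9 are p1 = 0.44, p2 = 0.22, CV = 0.3, m = 50 and alpha 0.05, taken as two-sided.

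- Within-cluster term: (0.2464 + 0.1716)/50 = 0.00836
- Between-cluster term: 0.09 × (0.1936 + 0.0484) = 0.02178
- c = 1 + 7.849 × 0.03014/0.0484 = 5.89, so 6 clusters per arm, as stated.

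With the seven clusters per arm actually used, power at a single round is 87% for m = 50, 85% for m = 40, 81% for m = 30 and 78% for m = 25. The between-cluster term dominates, so losing households costs little power until clusters fall below about 30.

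**The case against.** The strongest reply is that the rule applies to both arms, that child substitution will keep most households in, and that nothing in the article shows differential absence. Equal exclusion with the same prevalence ratio leaves a null effect null. Even the less favourable illustration gives 0.86, a modest shift beside the design odds ratio of about 0.36 (44% versus 22%). All of this stands. It limits the size of the problem but gives no reason to keep the rule.

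Several stronger readings are tempting and should not be adopted:

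- **That 2.4 contradicts the substitution rule in 2.2.2.** It does not. Substitution works at child level and exclusion at household level. They nest, and substitution probably reduces how many households are caught.
- **That 2.4 contradicts 2.14.3.** The reference there to all post-intervention surveys names the rounds in the model, not the households.
- **That data were deleted.** The text says only that they were left out of the analyses, so the records may still exist.
- **That about half the sample is lost.** This needs a single miss to disqualify, at absence of 10% or more per round. Everyday use of the word 'consistently' suggests repeated absence, and absences probably concentrate in a few households.
- **That the mixed model removes the problem once all data are used.** It accommodates unequal numbers of rounds, but its estimates are valid only if absence is ignorable given the model.

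A numerical threshold might be given in a fuller protocol or analysis plan. That would answer the vagueness, not the post-randomisation exclusion itself.

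**Conclusion.** The point holds as a post-randomisation exclusion with possible, undemonstrated bias in the primary comparison and an unnecessary loss of valid results. Its size is unknown. Under the assumptions shown, between about 2% and 56% of households could be excluded, depending on absence and on how many misses disqualify. A null odds ratio could move to about 0.86 or 1.14 if exclusion were 10% versus 30% and related to infection. Bias is the main issue, wasted data the second and power a distant third. The stated six clusters per arm reproduce and are not in dispute.

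**What to change.** Replace the rule in section 2.4 with an analysis-set definition for the primary analysis. It should include every mRDT result collected after the intervention from a child who meets the Table 1 criteria in a registered household. Each result is analysed in the arm to which the cluster was randomised, whatever the number of rounds attended, and up to any withdrawal of consent. Keeping Table 1 matters, so that visiting children or those outside the age range do not enter.

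In addition:

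- restore records already left out, where they still exist;
- report missed rounds and households affected, by arm;
- define 'consistently available' numerically and show that subset only as a sensitivity analysis;
- state that the mixed model assumes absence is ignorable given its terms, so the change reduces selection bias but may not remove it.

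The cost is revised wording, re-inclusion of existing records and one extra table. No new data are needed, and the article's trial status says that statistical evaluation is still under way.

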### Monitoring and maintenance of 3D-WDS installations

2.5

The distribution of 3D-WDS was followed by monitoring and observation of the fully installed window screens at 10 weeks intervals. The fibre-mesh and cone structures of the 3D-WDS were inspected for any damage, and surveys were conducted to record data on their conditions at the time of inspection. The wooden frame of the windows was also examined, and the fit of the window within the wall opening was checked. The houses underwent inspections, and household members were questioned about the use of curtains or other materials to close windows, known reasons for any damage and whether attempts were made to fix any damage. The trial staff repaired any damage to the fibre-mesh, or the cone structures observed during the inspections as well as during the entomological and epidemiological surveys.

### Integration of standard malaria control practices

2.6

The standard practice of clinical management of malaria and the management of mosquitoes within the community (such as LLINs and IRS) were not withheld in either study group. However, these practices were documented during the baseline demographic survey and household surveys conducted post-intervention. Children who tested positive in malaria rapid diagnostic tests (mRDT) tests during both the baseline and follow-up were administered a 3-day course of **artemether-lumefantrine (ALu) (Coartem®)**. Additionally, participants were encouraged to continue using LLINs and were not instructed to refrain from using alternative vector control methods (such as coils, sprays and repellents). This approach allowed for an assessment of the impact of using 3D-WDS, while assuming that all other vector control measures remained in place for malaria prevention.

### Outcomes

2.7

The primary and secondary outcome measures of this study are outlined in Table 2.

**Table 2 tbl2:** Study outcome, analysis, and collection method.

Outcome	Method	Frequency
**Primary outcome**		
Malaria prevalence	mRDT	Cross-sectional surveys at baseline and 10, 20, 30, 40 and 50 (±2) weeks post installation
**Secondary outcomes**		
Anaemia	Hemocue analyser	same as above
Indoor mosquito densities	CDC-LTs	same as above
Entomological inoculation rate	RT-PCR/CDC-LTs	same as above
Community perception and acceptability	FGD's and interviews	Cross-sectional surveys at 30, 40 and 50 (±2) weeks post installation

**Table 3 tbl3:** Study timeline.

	Apr–May 2019	June–Aug 2019	Sep 2019–Mar 2020	Apr 2020–Jun 2021	Jul–Oct 2021
1. Preparatory Phase					
Study area mapping/on-site visits	X				
Candidate village selection	X				
Community engagement/Sensitization	X				
Enrolment and Informed consent	X	X			

2. Baseline surveys					
Sociodemographic survey		X			
Entomological survey		X			
Malariometric survey		X			
Insecticide resistance survey		X			

3. Enrolment					
Cluster selection for cRCT			X		
Workshop training for carpenters and technicians			X		
Installation of the 3D-WDS			X		
Distribution of LLINs			X		

4. Follow-up surveys					
Epidemiological				X	
Entomological				X	
Community perception and acceptance				X	
Intervention monitoring and repairs				X	

5. Close-out					X

### Participant timeline

2.8

The study spanned 2 years and 7 months (April 2019 to October 2021). The initial 6 months were dedicated to site selection, community engagement and the baseline survey. An additional 7 months were allocated for cluster formation and randomization, training of installers, installation of the 3D-WDS and distribution of LLINs. The cRCT itself lasted approximately 12 months, followed by a 3-month close-out stage.

The baseline survey began in May 2019, alongside community sensitization and a sociodemographic survey. Baseline entomological and epidemiological surveys were conducted in parallel during June and July 2019. Insecticide resistance surveys were carried out shortly after the long rainy season, between July and August 2019.

Cluster formation and randomization occurred in late August 2019, followed by the recruitment of installers and workshop training for 3D-WDS installation in September 2019. The installation process took 5 months (October 2019 to February 2020), and LLINs distribution occurred in early March 2020.

Epidemiological and entomological follow-up assessments were conducted in parallel through repeated cross-sectional surveys from April–May 2020 to June–July 2021, at intervals of 10, 20, 30, 40 and 50 (±2) weeks post-intervention. The epidemiological team visited one cluster per day during each follow-up survey (14 days for 14 clusters), examining children for malaria infection and anaemia. Entomological surveys involved randomly selecting 24 houses per cluster over six nights, with samples collected from four houses each night.

Ancillary social studies were conducted through FGDs and household interviews at 30, 40, and 50 (±2) weeks post-installation to assess the community's acceptance of the 3D-WDS. Screen integrity, maintenance and durability were also evaluated during these surveys.

The schedule of pre-intervention activities, baseline cross-sectional and post-intervention follow-up surveys are outlined in the table below (Table 3).

